**Inclusion criteria**

- Registered with a participating practice
- Age 40 – 60 on date of consent
- Presence of any one (or more) of the following risk factors
  - Depression – previous history OR active episode of minor depression as recorded on medical record – ***IF*** GP deems patient fit to participate
  - Diabetes (diagnosis e.g. on a diabetes disease register)
  - Hypertension (as per national guidelines)
  - Obesity (BMI of 30.0 or above)
  - Current smoker
  - High cholesterol (as per national guidelines)
  - Coronary heart disease (diagnosis e.g. on a CHD disease register)
  - Self reported sedentary lifestyle
  - Self reported lack of cognitive stimulation
- Medically stable
- Literate in language of the partner country where patient is recruited (English/Dutch/French as appropriate).
- Access to the internet in order to communicate by email and access information online.

**Exclusion criteria**

- Active episode of **major** depression, if GP deems patient too severely ill to participate, recorded in medical record or assessed using a validated assessment score e.g. HADS
- People who are unable to give informed consent
- People who have dementia

**Assessment of eligibility.**

Research teams, practice staff or a proxy (e.g. the Scottish Primary Care Research Network) will review general practice medical records using the above inclusion and exclusion criteria to identify potentially eligible patients and invite them to take part in In-MINDD. This process is illustrated in Figure 1.

As an alternative route of recruitment, practices will display flyers describing the In-MINDD feasibility study. Patients who believe they are eligible can then ask their GP or practice nurse for more information about the study. However, they must then meet the eligibility criteria to be considered for the study.

If recruitment through practices proves difficult, then ethical approval will be sought to recruit participants directly.

**Figure 1. Identification of eligible patients and randomisation into In-MINDD.**

**Assessment of eligibility.**

1: Conducted in the practice based on age; medical stability and presence of one or more IN-MINDD risk factors which are readily available to practices e.g. age band and smoker; age band, diabetic and smoker.

In Scotland: Practice with support of SPCRN to invite patient to participate.

France, Ireland, theNetherlands: Practice or research team to invite patient to participate.

Or

2: Responds to poster/flyer in GP practice, discusses with GP or practice nurse and then contacts researcher to discuss eligibility.

**Excluded.**

Don’t meet initial inclusion criteria

Declined to participate

Other reason

**IN-MINDD arm**

**Control arm**

**Randomisation.**

Stratified by country and by practice.

**Excluded.**

Don’t meet initial inclusion criteria

Declined to participate

Other reason

**Recruitment and baseline meeting.**

Verification of eligibility by researcher.

Informed consent.

Baseline data collection, by completion of IN-MINDD profiler.

1. ***Interventions***

The In-MINDD CONSORT diagram is shown in Section 13.

***11a. Interventions for each group.***

**IN-MINDD baseline data collection meeting.**

All participants expressing interest in the study will receive an information pack about the study after which they can contact the IN-MINDD researcher, who will then arrange a baseline meeting. At this meeting, the researcher will inform them about the trial and review their eligibility to participate. If the patient is eligible and is willing to proceed, informed consent will be obtained.

Participants will be assigned a unique log-in to the In-MINDD site, which they should use each time they access the on-line environment. Access to the support environment will be blocked until after randomisation, ensuring that only those randomised to the In-MINDD intervention can access the support environment.

Following consent, the researcher will go through the baseline data collection with the patient using the IN-MINDD risk profiler.

Data on variables identified as risk factors but not held routinely in GP records (e.g. cognitive activity; physical ability) will be collected at this meeting.

**Baseline data collection**

Baseline data will be collected using the In-MINDD profiler. This has been purposely designed and developed for the In-MINDD project by the project team. The data collected via the profiler includes the following:

• Background information about participants (such as age, sex, marital status, employment status, education attainment, level of occupational attainment, and living arrangements),

• Information about the participant’s health.

• Information about family medical history (i.e. dementia, cardiovascular disease and diabetes mellitus)

• Information about alcohol consumption and current and past smoking habits

While most of this will be self-completed, some clinical data (e.g. blood pressure, cholesterol level, verification of diagnosis of cardiovascular disease and diabetes), will be provided by the GP using a short pro-forma. These clinical data will either be given by the GP to the research participants who will input the data themselves (e.g. the process in Ireland) or be sent by the GP to the research team who will input the data after the baseline meeting (e.g. the process in Scotland). Patients will be informed of this at the baseline meeting.

The In-MINDD profiler will also collect data on participants’ mood, physical activity, cognitive activity and diet via four validated instruments, which have been carefully selected and adapted where necessary.

The four instruments are:

• Center for Epidemiologic Studies Depression Scale (CESD), a well known and widely used short 20-item self-report scale, created by Radloff^9^, and designed to measure symptoms associated with depression in the general population;

• European Prospective Investigation into Cancer and Nutrition (EPIC) Physical activity questionnaire, a self-administered questionnaire, which assesses physical activity in current occupation and in leisure and household domains in a typical week over the past year^10^;

• Adapted Cognitive Reserve Index questionnaire (CRIqadapted), a short instrument developed in Italy by Nucci et al^11^. It is based on a literature review of the most relevant sources from the cognitive reserve literature and is a compound measure of formal and non-formal education, occupational activity and frequency of participation in leisure time activities over an individual’s adult life i.e. since the age of 18);

• MEditerranean Diet Adherence Screener (MEDAS), a brief dietary assessment instrument that was developed in Spain for the PREDIMED trial^12^. It is a 14-item instrument that measures adherence to a Mediterranean diet enhanced with olive oil and nuts. Some minor adaptations have been made to the MEDAS instruments to make it suitable for use in non-Mediterranean countries such as Ireland and Scotland. The MEDAS instrument has been adapted for use online.

Participants will be asked to complete the questions in the profiler, which takes approximately 15 to 20 minutes.

Once the profiler has been completed, participants will be randomised to either the IN-MINDD or control arm of the trial.

At the baseline meeting (and before randomisation), research participants may also be invited to complete a Stroop test. It is intended to use the Luminosity Stroop test, a web-based platform (permission pending) to measure response inhibition, which is an executive function. Performance on the Stroop task will not be used for computing the In-MINDD lifestyle for brain health score/profile and will not influence it. The purpose of including the Stoop test is exploratory. The aim is to examine the relationships between cognitive reserve, executive function and LIBRA score, since research suggests that EF is predictive of cognitive decline.

**Randomisation**

Participants will be randomised in equal proportions to either (i) the In-MINDD arm or (ii) the control arm of the trial. Randomisation will be conducted by the Robertson Centre for Biostatistics, University of Glasgow and will be stratified by country and by practice. Following completion of the profiler, the researcher will access the randomisation sequence either on-line or via telephone. The research team will then write to the patient to inform them of their allocation to either the In-MINDD or control arm of the trial.

**In-MINDD arm of trial.**

Participants in the In-MINDD arm will receive a letter telling them that they have been allocated to the In-MINDD arm of the trial and they should contact their GP or practice nurse and arrange an appointment, in order to discuss their Lifestyle for Brain Health (LIBRA) score and profile and personalised plan. This will be presented to participants as an overall risk score, in visual form, as well as a breakdown of the risk factors where they are doing well (e.g. alcohol consumption within recommended levels) and the risk factors where lifestyle changes are needed to improve their overall LIBRA score, e.g. smoking and lack of physical activity (see Appendix xx). This letter will also give them a link to the In-MINDD system, where they will be able to access their on-line LIBRA profile and the In-MINDD on-line support environment.

Participants will be asked to attend their general practice for an appointment with either the GP or practice nurse, who will talk them through their profiler result and personalised plan. If this is problematic, for example in Ireland a GP consultation typically costs patients €50-60, participants will be sent the information and a telephone consultation offered instead or participants can choose not to discuss the LIBRA score and profile with their primary care providers.

Participants will then be free to access and use information held in the In-MINDD online support environment. Examples of activities that might be suggested include making changes to diet to aid weight reduction, or increasing the amount of physical activity done; or taking up a new activity, such as learning a language. Participants will be able to access advice and support about these activities from the In-MINDD online system and invited to set goals for health-related behaviour change. During this time, they will receive email reminders about their targets and goals and advice offered about progress.

At three months, participants will be asked to complete an on-line questionnaire about risk factor(s) they have selected and the steps and actions they have taken, if any, to reduce that or those risk factors. This questionnaire will address risk factors they selected, what they have learned about reducing that risk factor, what steps/actions they took to follow the advice given, how they have accessed those activities and how often and whether they are still participating in those activities. They will also be asked if they would be willing to be interviewed about their experience so far in In-MINDD. In addition, use of the In-MINDD support environment will be monitored remotely, e.g. how often they access the systems; for how long; and what sites they visit.

After six months participants will meet with the researcher or practice nurse again and update their information on the In-MINDD system in order to generate a final LIBRA score and profile.

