| Intervention(s) | Intervention: Participants given personalised Lifestyle for Brain Health (LIBRA) score and profile based on their modifiable risk factors and access to In-MINDD on-line support environment. |
|  | Control: Generalised health information. Personalised Lifestyle for Brain Health (LIBRA) score and profile based on their modifiable risk factors and access to In-MINDD on-line support environment given to control group at end of study. |
| Key inclusion & exclusion criteria | Inclusion criteria:   - Registered with a participating practice - Age 40 – 60 on date of consent - Presence of any one (or more) of the following risk factors   - Depression – previous history OR active episode of minor depression as recorded on medical record – ***IF*** GP deems patient fit to participate   - Diabetes (diagnosis e.g. on a diabetes disease register)   - Hypertension (as per national guidelines)   - Obesity (BMI of 30.0 or above)   - Current smoker   - High cholesterol (as per national guidelines)   - Coronary heart disease (diagnosis e.g. on a CHD disease register)   - Self reported sedentary lifestyle   - Self reported lack of cognitive stimulation - Medically stable - Literate in language of the partner country where patient is recruited (English/Dutch/French as appropriate). - Access to the internet in order to communicate by email and access information online. |
|  | Exclusion criteria:   - Active episode of **major** depression, if GP deems patient too severely ill to participate, recorded in medical record or assessed using a validated assessment score e.g. HADS - People who are unable to give informed consent - People who have dementia |
| Study type | A multi-centre, primary care-based, investigator-blinded, randomised 6-month feasibility trial |
| Date of first enrolment | July 2014 |
| Target sample size | 150 per country; 600 in total |
| Recruitment status | Pending |
| Primary outcome | Global dementia risk score |
| Secondary outcomes | Change in individual risk factors |

1. ***Roles and responsibilities***

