***Control arm of the trial.***

Participants in the control arm will receive a letter from the researcher telling them they are in the control arm; they will receive generic health information material e.g. on smoking cessation, increasing physical activity. Participants in the control arm will be asked to complete an on-line questionnaire at three months. (In order to maximise follow up rates participants who don’t complete the on-line questionnaire will be offered a telephone alternative.) They will be informed that we will contact them towards the end of the trial period, to identify anyone who may wish to be interviewed. At the end of the trial period they will meet again with the researcher and complete the profiler. They will receive a copy of their LIBRA score and profile and will be given access to the In-MINDD on-line support environment.

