**Summary schedule of assessments**

| **In-MINDD arm of trial** | **Control arm of trial** |
| --- | --- |
| IN-MINDD baseline data collection meeting with researcher  (Eligibility checked, consent obtained, baseline data collected) – 1 hour | IN-MINDD baseline data collection meeting with researcher  (Eligibility checked, consent obtained, baseline data collected) – 1 hour |
| Participants receive letter informing which arm of the trial they are allocated to. | Participants receive letter informing which arm of the trial they are allocated to. |
| Participants access In-MINDD online support site and views LIBRA score. | Participants receive printed generic health information |
| Participants attend GP practice to discuss profiler result and personalised plan. |  |
| During this six month period participants are invited to access In-MINDD support environment and set goals for health related behaviour change. |  |
| At three months participants are asked to complete an online questionnaire | At three months participants are asked to complete an online questionnaire |
| After six months participants meet with researcher or practice nurse to update information and receive a final LIBRA score | After six months participants meet with researcher or practice nurse to update information and receive a final LIBRA score |

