**Six month follow-up**

Meet researcher; complete profiler; receive old and new LIBRA score & profile

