***17a. Trial blinding***

The trial is single-blinded; patients, practitioners and the researcher conducting qualitative research will know the arm to which patients are allocated, however the statisticians conducting the quantitative analysis will be blinded to study allocation.

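### The protocol describes six-month collection of the primary outcome in three incompatible ways, one of them arm-dependent, and its investigator-blinded label is unsupported

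*Protocol*

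**What the plan says.** The primary outcome is the global risk score (section 12), generated from the In-MINDD profiler. Its collection at six months is described in three places.

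- Section 11a, separately by arm. In-MINDD arm: "After six months participants will meet with the researcher or practice nurse again and update their information on the In-MINDD system". Control arm: "At the end of the trial period they will meet again with the researcher and complete the profiler".
- Summary schedule of assessments, the same cell in both columns: "After six months participants meet with researcher or practice nurse to update information and receive a final LIBRA score".
- CONSORT diagram in section 13. One six-month box reads "Meet researcher; complete profiler; receive old and new LIBRA score & profile". The other also has a meeting with the researcher and completion of the profiler; it differs only in that the new score alone is handed over.

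On the nurse's earlier part in the In-MINDD arm, section 11a says: "Participants will be asked to attend their general practice for an appointment with either the GP or practice nurse". That person goes through the profiler result and the plan with the participant.

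On blinding, the synopsis gives the study type as "A multi-centre, primary care-based, investigator-blinded, randomised 6-month feasibility trial". Sections 8 and 17a state that participants, practitioners and the qualitative researcher know the allocation, and then: "however the statisticians conducting the quantitative analysis will be blinded to study allocation".

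**The concern.** Four country teams will work from this protocol, and they cannot follow all three descriptions. A team that follows the arm narratives may send In-MINDD participants to a practice nurse and controls to the researcher. A team that follows the schedule may use nurses in both arms, but only in the In-MINDD arm can that nurse be the person who gave the advice.

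Most profiler items are self-completed (section 11a, baseline data collection) by people who know their allocation. Who sits with them while they answer can affect the answers. If that differs by arm, the difference goes into the treatment estimate. Analysis by intention to treat, adjustment for the baseline score and a blinded statistician (sections 17a and 20) all act after the data have been collected and cannot remove it.

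The synopsis label adds to the problem. A reader who takes it at face value will assume that the people collecting outcomes do not know the allocation, and the body of the protocol does not provide for that.

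**Working it through.** No figure in the protocol can be reproduced for this point, so the check is a comparison of the passages, followed by one illustration with assumed inputs.

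**1. Six-month collection, side by side**

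| Place | In-MINDD arm | Control arm |
|---|---|---|
| Section 11a, arm narratives | researcher or practice nurse; update | researcher; complete the profiler |
| Summary schedule | researcher or practice nurse; update | researcher or practice nurse; update |
| CONSORT diagram, section 13 | researcher; complete the profiler | researcher; complete the profiler |

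The first row differs by arm. The second and third are each symmetric but disagree on who may attend and on the verb. Section 18 adds that completion of the profiler is repeated at the end of the trial, without distinguishing arms.

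**2. Can the collector be the adviser?** In the In-MINDD arm the discussion of score and plan is with the GP or practice nurse. The control arm has no such planned contact during the six months. The first two rows therefore allow the adviser to collect the outcome in one arm only. The diagram does not.

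**3. Is anyone who collects outcomes blinded?** Section 17a names the statisticians and nobody else as blinded. Under section 16c the researcher who has collected the baseline data assigns the arm. Under section 11a the research team writes to participants with their allocation, and controls meet the researcher again at the end. Section 5d points the other way: the steering committee is unblinded, and for that reason has no members from the other partner countries. That suggests some wish to keep those teams blind, but sections 11a and 16c do not deliver it. No section provides a blinded outcome collector.

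**4. Illustration (assumed shift).** Let *b* be the net shift, in SD units, in the In-MINDD arm mean that comes from collection alone. It enters the between-arm difference one for one. If only a share *q* of the arm is affected by a shift *s*, then b = q × s.

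- Against the effect sizes in section 14: 0.05/0.2 = 25% and 0.10/0.2 = 50%; 0.05/0.187 = 27% and 0.10/0.187 = 53%.
- False-positive rate with no true effect, 300 per arm (600 in total, equal allocation), two-sided alpha 0.05 (assumed, not stated in the protocol), unadjusted comparison: SE = √(2/300) = 0.0816; rate = Φ(b/SE − 1.96) + Φ(−b/SE − 1.96).
  - b = 0.05: b/SE = 0.612; rate = 0.094.
  - b = 0.10: b/SE = 1.225; rate = 0.232.
- If half the arm were affected by s = 0.10, then b = 0.5 × 0.10 = 0.05 and the rate is again 0.094.

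These figures show sensitivity only. Nothing in the protocol supports a particular *b* or its sign.

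**The case against.** The strongest reply is that the protocol does not establish different collection in the two arms. The schedule has identical cells, the diagram names the researcher for both arms, and section 18 repeats the profiler for everyone. That is right. A reader might infer from section 11a alone that the outcome will be collected differently; the documents leave the matter unsettled.

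Four further inferences are tempting and should not be drawn.

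- That updating means editing displayed baseline answers in one arm. No section says old answers are shown, and the schedule uses the same verb for controls.
- That the bias would favour the intervention. Wanting to please an adviser would exaggerate change, while anchoring on earlier answers would shrink it. The net sign is unknown.
- That the controls-only wording at three months, "complete the on-line questionnaire will be offered a telephone alternative", affects the primary outcome. It concerns a different questionnaire.
- That blood pressure, cholesterol and diagnoses will be refreshed unequally. The GP form is described for baseline only, and the In-MINDD appointment is for discussion, may be by telephone and may be declined. The protocol does not say where six-month clinical values come from, and silence is not evidence of imbalance.

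It can also be said that a nurse as both adviser and collector is only a possibility, that self-report by unblinded participants remains whatever is done, and that section 8 makes feasibility the principal aim. These points lower the severity but do not remove the contradiction. Section 7 lists comparative effectiveness as the first trial objective, and section 14 says the sample is sufficient to show an effect.

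**Conclusion.** The point holds as an inconsistency that permits arm-dependent measurement, not as proof that measurement will differ. Three descriptions of the primary outcome visit conflict. Two of them allow the In-MINDD adviser to collect the outcome with no equivalent among controls.

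The synopsis label is not supported by sections 8, 16c and 17a. It would go too far to state that every investigator is unblinded: section 17a does not classify all of them, and section 5d hints at an intention to blind partner teams. The accurate statement is that only the statisticians are named as blinded, and that the researcher assigning the arm cannot be.

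Size and direction of any bias cannot be derived. The 0.05 to 0.10 SD range is an assumption, and the resulting 9% and 23% false-positive rates depend on it and on a two-sided 5% test. This should be fixed; it does not by itself invalidate the design.

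**What to change.** Adopt one six-month procedure for both arms, following the CONSORT diagram: the participant completes the full profiler at a meeting with the researcher, before any score is shown, and the clinical inputs come from the same source in both arms. Align both arm narratives in section 11a and the summary schedule with it.

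Replace the investigator-blinded wording in the synopsis with a description that matches section 17a (participants and practitioners unblinded, statisticians blinded). Reconcile it with the remark on partner countries in section 5d and with the researcher's role in section 16c, and state whether the six-month collector knows the allocation.

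The cost is mainly wording. Completing the profiler takes 15 to 20 minutes by the protocol's own estimate. Dropping the nurse option reduces scheduling flexibility and moves any visits planned for nurses to the researcher. Using the same source for clinical inputs does not require a new form; repeating the GP form for everyone would be one way, at up to 600 further returns, and is not needed to resolve this point. The change has to be made before the first six-month visit, because outcomes collected unequally cannot be corrected in the analysis.
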